### Planned intervention

2.7

All study participants will receive initial resuscitation in the delivery room or operating room following the latest European Resuscitation Council Guidelines for newborns (16), which dictate whether non-invasive or invasive ventilation should be administered. Subsequently, they will be transported to the NICU using a transport incubator. Throughout ventilation and transportation, a T-piece resuscitator will be utilized to provide either non-invasive or invasive respiratory support (Initial parameters: PEEP = 6 cmH2O, PIP = 15–20 cmH2O, FiO_2_≤0.4) in order to maintain the patient's target oxygen saturation. If the target oxygen saturation is not achieved, PEEP and FiO_2_ can be upregulated, but in order to avoid pneumothorax, PEEP should be controlled at ≤8 cmH2O (2). Our NICU implements the “golden one-hour” management for premature infants (17, 18). Premature infants with successful recovery will be transferred to the NICU ward within 15 min and reach a relatively stable state shortly after birth. Upon admission to the ward, all preterm infants will be randomly assigned to either the ultrasound or control group.

#### Ultrasound group

2.7.1

Lung ultrasonography will be performed within 1 h of admission, followed by lung ultrasound scoring (refer to Figure 2 for the segmentation and scoring methods). In the case of different score patterns in the same area, the worst will be selected. If the lung ultrasound confirms RDS and LUS is more than 8, a full dose of PS will be promptly administered at 200 mg/kg (Poractant Alfa, Curosurf®). If the lung ultrasound does not indicate RDS or if LUS is 8 or less, clinical monitoring will continue. Should the clinical criteria for NRDS be met, a full dose of PS will be administered at 200 mg/kg (Poractant Alfa, Curosurf®). In terms of the administration method, less-invasive surfactant administration (LISA) will be employed for infants in a non-invasive ventilation state, while those in an invasive ventilation state will receive PS via endotracheal tube. Lung ultrasound and scoring will be repeated 4–10 h post the first PS dose administration (with scoring results withheld from the clinical team). Repeated PS administration will occur if the criteria are met, with lung ultrasound scoring conducted prior to each administration (with scoring results withheld from the clinical team). Repeated PS administration will be completed via endotracheal tube.

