#### Control group

2.7.2

In cases where clinical diagnosis confirms NRDS, PS will be administered at a dosage of 200 mg/kg (Poractant Alfa, Curosurf®). LISA will be employed for infants in a non-invasive ventilation state, while those in an invasive ventilation state will receive PS via endotracheal tube. If clinical manifestations do not meet the diagnosis of NRDS, PS will not be administered.

All enrolled infants will undergo lung ultrasound scoring at 24 h, 3 days, 7 days, 14 days, 28 days, and 36 weeks CA (prior to discharge) (with scoring results withheld from the clinical team).

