Clinical diagnostic criteria for NRDS: Within 24 h of birth, if an infant experiences respiratory distress, they are supported with nasal intermittent positive pressure ventilation (NIPPV) or nasal continuous positive airway pressure (NCPAP). Diagnosis of NRDS occurs when the infant exhibits progressively worsening symptoms, such as a respiratory rate of more than 60 breaths/min, grunting, nasal flaring, intercostal retractions, and/or cyanosis, along with a peripheral capillary oxygen saturation (SpO2) of 85% or less, a Silverman Anderson Score (SAS) of more than 5, or an hourly increase in SAS by more than 2 while the FiO_2_ is more than 0.4 (or >0.3 for those with a GA<28 weeks). These symptoms may or may not be accompanied by typical chest x-ray findings.

Indications for repeated use of PS include the following: within 72 h after birth (that is, 10–70 h after the initial PS administration), if respiratory distress persists, chest x-ray findings confirm the diagnosis of NRDS, and other causes of respiratory difficulties have been excluded.

Indications for endotracheal intubation and invasive mechanical ventilation within 72 h after birth include: (1) severe respiratory acidosis indicated by blood gas analysis 2 h after the initial PS administration (PaCO2 >65 mmHg, pH <7.20); (2) hypoxemia, with an FiO_2_ of more than 0.4 and an SpO2 of less than 0.85; (3) recurrent episodes of respiratory pauses, more than 3 episodes of spontaneously recoverable respiratory pauses per hour, or one episode of respiratory pause requiring positive pressure ventilation within 24 h; (4) an increase in SAS by more than 2 per hour, or an SAS of more than 5 persisting for more than 2 h; (5) pulmonary hemorrhage; (6) respiratory or cardiac arrest requiring endotracheal intubation for resuscitation; and (7) required by NICU physicians for respiratory support to ensure the infant will receive optimal treatment. Criteria for extubation include an FiO_2_ of less than 0.3 and a mean airway pressure (MAP) of less than 7–8 cmH2O.

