### Outcome measures

2.9

The primary outcome measure for this study is the duration of mechanical ventilation (both invasive and non-invasive) during hospitalization in the ultrasound and control groups. Secondary outcome measures encompass: (1) the utilization rate of PS in both groups; (2) the proportion of infants receiving the first dose of PS early (within 3 h after birth) and the time from birth to the initial PS administration; (3) the oxygen concentration and the worst oxygenation index (OI) at different time points following PS administration; (4) LUS at various intervals following PS administration (at 3 days, 7 days, 14 days, 28 days, and before discharge/at 36 weeks CA; and (5) the incidence rates of major complications in preterm infants such as BPD, intraventricular hemorrhage (IVH), retinopathy of prematurity (ROP), and necrotizing enterocolitis (NEC).

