### Sample size calculation

2.12

With the duration of mechanical ventilation as the primary outcome measure for both groups, we anticipate that patients in the conventional treatment group will require an average of 96 ± 12 h of respiratory support based on previous departmental data. It is expected that integrating ultrasound diagnosis will promptly improve respiratory function, reducing the mechanical ventilation duration to an average of 86 ± 12 h. To compare the difference in mechanical ventilation duration between the groups, a two-sample independent *t*-test will be employed, setting α at 0.05 and ensuring a power of 80%. With a 1:1 ratio between the groups, sample size estimation using PASS15 indicates that each group will require 24 patients, totaling 48 patients. Considering the potential risk of underestimating sample size due to low effect size and dropout rates, the actual sample size will be 60 patients (48 ÷ 80% = 60), with 30 patients in each group.

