Based on prior research, this study protocol has been refined and improved in the following aspects: (1) Patient selection: very preterm infants with a GA of less than 32 weeks will be selected. According to previous study reports, the incidence of NRDS increases gradually with a decrease in GA. The incidence of NRDS in extremely preterm infants (GA ≤28 w) has been reported to be 93%; however, even among late preterm infants at 34 weeks GA, 10.5% of patients were diagnosed with NRDS (29, 30). In preterm infants below 32 weeks GA, early postnatal respiratory distress can be caused by a variety of causes. Differential diagnosis through traditional imaging is not only less sensitive but also brings about the challenges of radiation exposure. Patients often have delayed application or overuse of PS owing to misdiagnosis. Our study will include this population as the research object, hoping to identify NRDS more accurately and guide PS application through non-invasive methods in the early stage. (2) The clinical application of LUS was optimized: most previous studies judge whether to use PS only according to LUS, ignoring the possibility that other diseases causing respiratory distress may be misdiagnosed as NRDS. The severity of lung lesions caused by different diseases cannot be compared in parallel by LUS. In our study, the researchers first diagnosed NRDS through lung ultrasound and then assessed the severity of NRDS according to LUS and guided the application of PS. The combination of qualitative diagnosis and semi-quantitative assessment was more reasonable. In the diagnosis of NRDS by pulmonary ultrasound, the lesions may appear in any lung field; the pulmonary ultrasound guidelines clearly indicate that the lung lesions of NRDS mainly appear posteriorly, and therefore, the examination of the posterior region should not be ignored (19). In previous studies, in order to avoid moving patients, only the anterior and lateral lung fields were examined and scored, which may affect the accuracy of results (25, 31). In our study, according to the pulmonary ultrasound guidelines for lung partitioning, the anterior, lateral and posterior lungs were comprehensively evaluated and the scores of each lung field were recorded; the final total score was then calculated, which will be more accurate than the calculations in previous studies. (3) Timing of lung ultrasonography: previous studies have limited time points for lung ultrasound assessments, usually within the first 24 h post-birth. However, in the early postnatal period, premature infants experience rapid changes in their conditions and may require repeated administration of PS. Therefore, in our study design, the ultrasound group will undergo multiple lung ultrasound examinations within the first hour after birth, 4–10 h after the initial PS administration, prior to subsequent PS administration, and at 24- and 72-h post-birth. This will be the highest frequency of lung ultrasound examinations among known studies of the same type, and this approach allows for better monitoring of early postnatal lung ultrasound dynamics. Additionally, follow-up lung ultrasonography will be conducted at 1, 2, and 4 weeks after birth, as well as before discharge, thereby providing a basis for prognostic assessment; (4) Treatment method: following the 2022 European Consensus Guidelines on the Management of Respiratory Distress Syndrome, NCPAP combined with LISA was identified as the preferred treatment for preterm infants with spontaneous breathing after birth (2). Therefore, in this study, for infants receiving non-invasive ventilation (NCPAP or NIPPV) and exhibiting spontaneous breathing, priority will be given to the LISA method to reduce the risk of airway injury. This study aims to combine non-invasive diagnosis methods with non-invasive treatment to reduce the requirement for early invasive operations after the birth of preterm infants.

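### The route for repeat surfactant is stated only for the ultrasound arm, so as written two infants meeting the same repeat criteria could be treated by different routes depending on arm

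*Protocol article*

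**What the plan says.** **Ultrasound arm (2.7.1).** The route first follows the type of support: "less-invasive surfactant administration (LISA) will be employed for infants in a non-invasive ventilation state", with the tube for infants already ventilated invasively. The paragraph then turns to later doses and closes with "Repeated PS administration will be completed via endotracheal tube".

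**Control arm (2.7.2).** "LISA will be employed for infants in a non-invasive ventilation state, while those in an invasive ventilation state will receive PS via endotracheal tube". No first-dose limit is attached, and repeat doses are not mentioned.

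**Both arms (2.8, Therapy).** "Indications for repeated use of PS include the following: within 72 h after birth", followed by the clinical and radiographic conditions. No arm is named and no route is given. The same section sets one extubation rule: "Criteria for extubation include an FiO_2_ of less than 0.3 and a mean airway pressure (MAP) of less than 7–8 cmH2O". It has no separate rule for an infant intubated only to receive a dose.

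**Discussion, item (4) on treatment method.** For spontaneously breathing infants on non-invasive ventilation, "priority will be given to the LISA method to reduce the risk of airway injury". Neither an arm nor a repeat-dose exception is named.

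**Outcomes.** The primary outcome (2.9) is "the duration of mechanical ventilation (both invasive and non-invasive) during hospitalization". Table 1 also lists invasive and non-invasive hours separately.

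**The concern.** The trial is meant to test whether an early scan improves the decision to give the first dose. Other treatment should follow the same rules in both arms. Section 2.5 goes some way to protect this, by withholding later scans so that they do not influence the second-dose decision. The route of that second dose, however, is written for one arm only.

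If staff follow the text literally, they know the allocation and can apply an arm-specific route. Some ultrasound-arm infants would then be intubated for a repeat dose when a comparable control infant might not be. The comparison of invasive hours would mix the effect of the scan with the effect of the route. The comparison of total hours could be affected too if intubation for a dose prolongs support overall.

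**Working it through.** **1. Comparison of the text.** Take an infant on non-invasive support who meets the repeat-dose indications in 2.8.

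| Place | Applies to | Route for a repeat dose |
|---|---|---|
| 2.7.1 | Ultrasound arm | Endotracheal tube, whatever the support |
| 2.7.2 | Control arm | Repeat dose not mentioned; the general rule, if extended to it, gives LISA |
| 2.8 | Both arms | None given |
| Discussion, item (4) | No arm named | LISA has priority if breathing spontaneously |

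Control infants can receive repeat doses, because the indications in 2.8 are shared. Nothing extends the tube sentence to them. The article does mark rules meant for everyone elsewhere: the scan schedule closing 2.7.2 is for all enrolled infants, and caffeine in 2.8 is for all participants. The tube sentence carries no such marker.

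**2. The plan's own figure (2.12).** Inputs: control mean and SD "an average of 96 ± 12 h of respiratory support"; ultrasound mean 86 h with the same SD; α 0.05 (taken as two-sided, since sidedness is not stated); power 80%; 1:1 allocation.

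- Difference: 96 − 86 = 10 h. Standardised difference: 10 / 12 = 0.833.
- Two-sample t-test: 23.6, so 24 per arm, with power 80.7%.
- Inflation: 48 / 0.80 = 60.

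The stated sample size reproduces and is not in dispute. The 10 h is the yardstick for what follows.

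**3. What a route difference could do to the primary outcome.** Let *r* be the share of ultrasound infants given a repeat dose by tube while on non-invasive support, and *h* the hours this adds to their **total** support. The ultrasound mean rises by *r* × *h*, and the net difference is 10 − *r* × *h*. The article gives neither quantity. The values below are assumptions chosen to show the range, with control infants taken to be unaffected.

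| *r* | *h* (h) | Shift (h) | Net difference (h) | Power at 24 per arm |
|---|---|---|---|---|
| any | 0 | 0 | 10 | 80.7% |
| 0.1 | 6 | 0.6 | 9.4 | 75.7% |
| 0.2 | 12 | 2.4 | 7.6 | 57.5% |
| 0.3 | 24 | 7.2 | 2.8 | 12.4% |

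The first row matters most. If hours only move from non-invasive to invasive, *h* = 0 and the primary outcome does not change, while invasive hours still rise. The range runs from nothing to most of the target difference, and nothing in the article narrows it.

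**The case against.** The strongest reply is that this is a drafting gap, not a planned difference. Section 2.7.2 is short, never mentions repeat doses, and places its route sentence straight after the initial treatment decision. Nearly the same sentence in 2.7.1 is followed by a separate rule for repeat doses, so there it governs the first dose. One rule may well have been meant for both arms, and a journal article may leave the detail to the full protocol. This stands to the extent that the control text is silent on repeat doses. A reader might infer that it prescribes LISA for them, but the article does not say so. It remains true that the article states a repeat-dose route for one arm, and for the other only a general rule without a first-dose limit. That is more than silence in both arms.

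A second reply is that the Discussion gives LISA priority, not exclusivity, and only for spontaneously breathing infants, in a passage that can be read as being about initial treatment. This stands too. The tube rule sits uneasily with that passage but does not flatly contradict it.

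A third reply concerns size. The primary outcome adds both kinds of hours, and no passage says that a dose by tube commits the infant to continued ventilation. Infants still in distress may already be intubated under the shared criteria in 2.8, so few may be affected. All of this stands.

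On data capture, Table 1 records support mode at every time point and both kinds of ventilation hours, which helps. It does not show the route of a repeat dose.

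**Conclusion.** The point holds as an inconsistency to be reconciled. As written, the repeat-dose route is fixed for the ultrasound arm and left open for control, where the general rule could lead to a different route. The difference would not depend on the first scan, and it bears directly on invasive ventilation hours.

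A reader might go further and infer that the primary comparison is biased by a definite number of hours, or that a benefit will be hidden or a harm created. The documents do not support that. The effect on total hours depends on an unreported repeat-dose rate, on whether control infants are in fact treated by another route, and on whether intubation for a dose lengthens total support. The hours and power figures shown are illustrations on assumed inputs. Nor do the documents show that the sponsor chose different routes by arm. Which route is right is a clinical matter and is not judged here.

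**What to change.** Reconcile 2.7.1, 2.7.2, 2.8 and item (4) of the Discussion so that a single repeat-dose route rule is stated once in the shared section 2.8 and applies identically to both arms. The content of the rule is for the sponsor to decide; the statistical requirement is only that it does not depend on arm. If the full protocol already contains such a rule, the article's wording should be brought into line with it.

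Add the route of every repeat dose to the data collected (2.10 lists the method for the initial dose only), and report repeat doses and their route by arm next to the invasive and non-invasive hours. A reader can then see whether the arms were treated alike.

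The cost is one sentence and one data field, with no extra infants, procedures or follow-up.

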**Figure 2 F2:**
[figure not shown]
Calculating lung ultrasonography scores. Segmentation: Each lung is divided into 3 regions (anterior L12/R12, lateral L34/R34, and posterior L56/R56), totaling 6 regions. Scoring: The higher the score, the more severe the condition, with a total score of 18 points. The detailed scoring criteria are as follows: (**A**) 0 points indicate normal lung ventilation, characterized by A-lines with sporadic B-lines; (**B**) 1 point signifies moderate reduction in lung ventilation, including fused B-lines and interstitial syndrome (B-line accumulation <50% of the lung field examined); (**C**) 2 points denote severe reduction in lung ventilation, with a small amount of localized subpleural consolidation (B-line accumulation ≥50% of the lung field examined; B-line covers more than half of the intercostal space); (**D**) 3 points represent extensive lung consolidation.

#### Control group

2.7.2

In cases where clinical diagnosis confirms NRDS, PS will be administered at a dosage of 200 mg/kg (Poractant Alfa, Curosurf®). LISA will be employed for infants in a non-invasive ventilation state, while those in an invasive ventilation state will receive PS via endotracheal tube. If clinical manifestations do not meet the diagnosis of NRDS, PS will not be administered.

All enrolled infants will undergo lung ultrasound scoring at 24 h, 3 days, 7 days, 14 days, 28 days, and 36 weeks CA (prior to discharge) (with scoring results withheld from the clinical team).

### Therapy

2.8

Lung ultrasound procedure: The lungs will be partitioned based on the six-region method in the pulmonary ultrasound guidelines. Each lung will be divided into three regions: anterior, lateral, and posterior lung area. To do this, the anterior axillary line and the posterior axillary line will be used as boundaries. Both lungs will be divided into a total of six regions (19). An ultrasound probe perpendicular to the intercostals will be used to scan each area from the top to bottom and score it. A score of 0–3 (as proposed by Bratet al.) will be assigned to each scan area based on the ultrasound detected pattern; in the case of different score patterns in the same area, the worst will be selected (Figure 2) (14).

RDS lung ultrasound diagnostic criteria: (1) Lung consolidation with air bronchograms: this is the most crucial ultrasound manifestation of RDS, characterized by: (i) The degree and extent of consolidation correlate with disease severity. Mild RDS may exhibit consolidation limited to the subpleural areas, appearing focal and small in scope, while severe RDS demonstrates expanded consolidation areas, extending into deeper lung fields; (ii) consolidation may be observed in different lung fields on bilateral lungs or restricted to certain intercostal spaces on one side; and (iii) air bronchograms present as dense, snowflake-like, or spot-like patterns, with the consolidation area showing heterogeneous hypoechoic areas that are easily distinguishable from surrounding lung tissue; (2) Abnormal pleural lines and disappearance of A-lines; (3) Non-consolidated areas show changes resembling interstitial syndrome; (4) Bilateral points: these may be present during the acute phase of mild RDS or the recovery phase of severe RDS; and (5) pleural effusion: infants may exhibit varying degrees of unilateral or bilateral pleural effusion (19).

Clinical diagnostic criteria for NRDS: Within 24 h of birth, if an infant experiences respiratory distress, they are supported with nasal intermittent positive pressure ventilation (NIPPV) or nasal continuous positive airway pressure (NCPAP). Diagnosis of NRDS occurs when the infant exhibits progressively worsening symptoms, such as a respiratory rate of more than 60 breaths/min, grunting, nasal flaring, intercostal retractions, and/or cyanosis, along with a peripheral capillary oxygen saturation (SpO2) of 85% or less, a Silverman Anderson Score (SAS) of more than 5, or an hourly increase in SAS by more than 2 while the FiO_2_ is more than 0.4 (or >0.3 for those with a GA<28 weeks). These symptoms may or may not be accompanied by typical chest x-ray findings.

Indications for repeated use of PS include the following: within 72 h after birth (that is, 10–70 h after the initial PS administration), if respiratory distress persists, chest x-ray findings confirm the diagnosis of NRDS, and other causes of respiratory difficulties have been excluded.

Indications for endotracheal intubation and invasive mechanical ventilation within 72 h after birth include: (1) severe respiratory acidosis indicated by blood gas analysis 2 h after the initial PS administration (PaCO2 >65 mmHg, pH <7.20); (2) hypoxemia, with an FiO_2_ of more than 0.4 and an SpO2 of less than 0.85; (3) recurrent episodes of respiratory pauses, more than 3 episodes of spontaneously recoverable respiratory pauses per hour, or one episode of respiratory pause requiring positive pressure ventilation within 24 h; (4) an increase in SAS by more than 2 per hour, or an SAS of more than 5 persisting for more than 2 h; (5) pulmonary hemorrhage; (6) respiratory or cardiac arrest requiring endotracheal intubation for resuscitation; and (7) required by NICU physicians for respiratory support to ensure the infant will receive optimal treatment. Criteria for extubation include an FiO_2_ of less than 0.3 and a mean airway pressure (MAP) of less than 7–8 cmH2O.

Criteria for discontinuation of non-invasive ventilation: (1) more than 72 h after birth; (2) a PEEP of 3–5 cmH2O or less during NCPAP, or an MAP of less than 6–7 cmH2O during NIPPV; (3) an FiO_2_ of 25% or less; (4) an SAS of less than 3; and (5) absence of respiratory pauses or bradycardia requiring stimulation for recovery. If all five conditions are met and sustained for over 24 h, discontinuation of non-invasive ventilation may be considered based on clinical assessment. If any of the following conditions arise after discontinuation of non-invasive ventilation, encompassing: (1) an FiO_2_ of more than 0.25 and an SpO2 of less than 85%; (2) an SAS of more than 3; or (3) three or more episodes of spontaneously recoverable respiratory pauses or bradycardia within 24 h, non-invasive ventilation will be reinstated. Reassessment for discontinuation of non-invasive ventilation will not be conducted until at least 48 h later.

All study participants will receive caffeine citrate within 24 h after birth to prevent respiratory pauses, with an initial loading dose of 20 mg/kg and a maintenance dose of 5–10 mg/kg per day.

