## Abstract

**Background:**

Bedside lung ultrasonography has been widely used in neonatal intensive care units (NICUs). Lung ultrasound scores (LUS) may predict the need for pulmonary surfactant (PS) application. PS replacement therapy is the key intervention for managing moderate to severe neonatal respiratory distress syndrome (NRDS), with early PS administration playing a positive role in improving patient outcomes. Lung ultrasonography aids in the prompt diagnosis of NRDS, while LUS offers a semi-quantitative assessment of lung health. However, the specific methodologies for utilizing LUS in clinical practice remain controversial. This study hypothesizes that, in very preterm infants [<32 weeks gestational age (GA)] exhibiting respiratory distress symptoms, determining PS application through early postnatal LUS combined with clinical indicators, as opposed to relying solely on clinical signs and chest x-rays, can lead to more timely PS administration, reduce mechanical ventilation duration, improve patient outcomes, and lower the occurrence of bronchopulmonary dysplasia (BPD).

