In existing studies, the utilization of LUS to assess NRDS often involves simplified adaptations from adult LUS systems. A unified standard for LUS assessment in neonates remains elusive (14, 15). Variations exist in the scoring locations and methods of LUS applied across different studies. Furthermore, a consensus on the threshold of LUS for PS application has yet to be established, hindering its widespread clinical application. Therefore, this study aimed to demonstrate, through a randomized controlled trial, that for very preterm infants (< 32 weeks GA) experiencing respiratory distress, determining PS application based on LUS combined with clinical indications can lead to more accurate NRDS diagnosis compared with traditional methods that rely on clinical indications and chest x-rays. Hence, this approach may facilitate the early and appropriate use of PS, within 3 h postnatally, thereby reducing mechanical ventilation duration, improving patient outcomes, lowering the incidence of BPD, and decreasing medical expenses. Furthermore, lung ultrasonography can partially substitute for chest x-rays in the diagnosis of early NRDS, significantly reducing early radiation exposure for patients.

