### Assessment points

2.6

The main assessment and recording of the infants’ indicators will occur at the following time points (Table 1).

**Table 1 T1:** Neonatal assessment chart.

Measure	Assessment point							
	Allocation within 1 h after birth	4–10 h after PS	24 h	3 days	7 days	14 days	28 days	36 weeks CA/discharge
LUS	×	×	×	×	×	×	×	×
Clinical index								
Silverman Anderson score	×	×	×	×	×	×	×	×
Respiratory support mode	×	×	×	×	×	×	×	×
Ventilator parameters	×	×	×	×	×	×	×	×
Medication use of PS	×		×					
Outcomes assessment								
NIV (hours)								×
IMV (hours)								×
Supplemental oxygen (days)								×
PS (%)								×
Early PS (%)								×
Birth to the application of 1st PS (min)								×
LOS								×
Costs associated with hospital care								×
Complications								
hsPDA (%)								×
BPD (%)								×
IVH (%)								×
NEC stage I or II (%)								×
ROP (%)								×

NIV, non-invasive ventilation; IMV, invasive mechanical ventilation; Early PS, pulmonary surfactant administered within 3 h after birth; LOS, length of stay; hsPDA, hemodynamically significant patent ductus arteriosus; IVH, intraventricular hemorrhages; BPD, bronchopulmonary dysplasia; NEC, necrotizing enterocolitis; ROP, retinopathy of prematurity.

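### The repeat-surfactant window in section 2.8 is given on two clocks as if they were the same, but their upper limits agree only for a first dose at 2 h after birth

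*Protocol article*

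**What the plan says.** The indications for a repeat dose are in section 2.8 (Therapy), which serves both arms. The timing condition reads "within 72 h after birth (that is, 10–70 h after the initial PS administration"). The first figure counts from birth and has only an upper limit. The second counts from the first dose and has a lower and an upper limit. The words linking them present the second as a restatement of the first.

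The time of the first dose is left open:

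- **Ultrasound group (2.7.1):** "Lung ultrasonography will be performed within 1 h of admission", and PS follows promptly if the scan confirms RDS and the score exceeds 8. Infants who do not meet that rule are watched and treated if they later meet the clinical criteria.
- **Control group (2.7.2):** PS is given when the clinical criteria are met. No time is set.
- **Table 1 footnote (2.6):** the early-dose category is defined as "Early PS, pulmonary surfactant administered within 3 h after birth". The proportion of infants dosed early is an outcome, so later first doses are expected.
- **Outcome measures (2.9):** "the time from birth to the initial PS administration" is a secondary outcome.

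**The concern.** A threshold that decides whether an infant may be treated again is stated twice, and the two statements give different answers for most first-dose times. Two clinicians following the same sentence could reach opposite decisions about the same infant.

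The disagreement grows with a late first dose, and first-dose timing is what the trial sets out to change. The Abstract's hypothesis is that the ultrasound strategy "can lead to more timely PS administration". Late doses, and so ambiguous cases, would then be more frequent among controls. Section 2.5 has clinicians aware of allocation, so nothing ensures that the sentence is read the same way in both arms.

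There is a possible route to the outcomes. Section 2.7.1 has repeat doses given through an endotracheal tube, the primary outcome counts invasive as well as non-invasive ventilation time, and oxygenation after PS is a secondary outcome. The disputed ages, from 72 h up to 94 h for a first dose at 24 h, also lie below the 96 h mean support that section 2.12 assumes for controls, so infants could still be on support at those ages.

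**Working it through.** **Inputs.** From section 2.8: upper limit on the birth clock, 72 h of age; limits on the first-dose clock, 10 h and 70 h. T is the time of the first dose in hours after birth. The values of T below are illustrative, because the document gives no distribution of first-dose times.

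**Reproducing the stated equivalence.** The first-dose clock closes at T + 70 h of age. Setting T + 70 = 72 gives T = 2. The equivalence therefore holds for the upper limit at T = 2 h and at no other time. The 10 h lower limit has no counterpart on the birth clock.

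**Gap between the upper limits.** Gap = (T + 70) − 72 = T − 2 h.

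**Window length if both limits must hold.** The window opens at T + 10 h of age and closes at the earlier of 72 and T + 70. Its length is min(72, T + 70) − (T + 10) = min(62 − T, 60) h.

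| First dose T (h) | First-dose clock closes (h of age) | Gap to 72 h (h) | Length if both limits hold (h) |
|---|---|---|---|
| 1 | 71 | −1 | 60 |
| 2 | 72 | 0 | 60 |
| 3 | 73 | 1 | 59 |
| 4 | 74 | 2 | 58 |
| 6 | 76 | 4 | 56 |
| 12 | 82 | 10 | 50 |
| 24 | 94 | 22 | 38 |

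**If only the first-dose clock applies,** the length is 70 − 10 = 60 h for every T, and what moves is the closing age in the second column.

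**If only the birth clock applies,** the time left after the first dose is 72 − T h: 70 h at T = 2 and 48 h at T = 24. Those two figures leave out the stated 10 h lower limit. With it, they become 60 h and 38 h, as in the table.

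**Example.** An infant first dosed at 12 h and assessed at 75 h of age is 63 h past the first dose (75 − 12). That is inside 10 to 70 h but outside 72 h after birth.

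**The case against.** The strongest reply is that 72 h after birth is the rule and the bracket is an approximate gloss for infants dosed early. For first doses up to 4 h the two limits differ by no more than 2 h. Timing is also only one of several conditions: a repeat dose further requires continuing distress, radiographic confirmation and exclusion of other causes. This limits the practical size of the problem. It does not remove the contradiction, because the sentence does not mark the bracket as approximate and first doses after 4 h are possible in both arms.

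A reader might go further and infer that the rule biases the comparison, with control infants losing or gaining eligibility systematically. The document does not support that, for five reasons.

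- The 24 h in the clinical criteria is not a period within which controls are diagnosed. The sentence begins "Within 24 h of birth, if an infant experiences respiratory distress" and goes on to respiratory support. Diagnosis depends on later worsening and carries no time limit, so T = 24 h is an assumption.
- Late first doses are not confined to one arm. Section 2.7.1 sends ultrasound infants who do not meet the scan rule to the same clinical criteria.
- Without first-dose times by arm, no between-arm difference can be calculated.
- The tube route for repeat doses is stated only under the ultrasound group. Section 2.7.2 gives no repeat route for controls, so the path to ventilation hours is less direct for the infants thought to be most affected.
- Some dependence on first-dose time would remain under any single clock. A birth clock shortens the time left after a late dose, and a first-dose clock moves the closing age. That follows from comparing strategies that differ in timing.

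**Conclusion.** The point holds as a minor internal contradiction in a treatment-eligibility threshold. The mismatch is exact arithmetic on two stated figures: T − 2 h, and zero only at T = 2 h. It is negligible for early first doses and reaches 10 h at T = 12 and 22 h at the illustrative T = 24. If both limits must hold, the window shrinks from 60 h for T ≤ 2 to 50 h at T = 12 and 38 h at T = 24.

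That controls will have more late first doses is the trial's own expectation, not an established fact. The size of any effect on the primary or secondary outcomes cannot be derived from the document, and the finding does not rest on one. Which limit is clinically appropriate is not judged here.

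**What to change.** Reconcile the two figures in section 2.8. Delete the words *that is*, which assert an equivalence that fails, and state either which limit governs or that both must hold. Apply the resulting window identically in both arms, and match the case report form to it by recording the times of birth, first dose and any repeat dose on the same basis. The choice of clock and limits belongs to the clinicians.

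The cost is one sentence and the matching form field. The change removes the contradiction, but not every dependence of eligibility on when the first dose was given.
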